### Glycoprotein capture

2.10

Glycoprotein capturing lectin column will be self-packed and connected to high performance liquid chromatography (HPLC) system for lectin affinity chromatography (LAC). Pooled human plasma from lung cancer patients will be loaded directly onto the column with mobile phase. The detailed affinity chromatographic method will follow the method section of the reference paper.^[43]^

### Trypsin digestion and deglycosylation with PNGase F

2.11

The selected proteins will be digested with sequencing grade trypsin for protein digestion and then with PNGase F for deglycosylation of glycoproteins. The detailed proteomics method will follow the method section of the reference paper.^[44]^ The PNGase F-treated peptide mixtures will be stored at −80°C until analyses.

### nLC-MS/MS methods for protein identification

2.12

The PNGase F-treated peptide mixtures from the 6 groups (LCEX, LCES, LCEG, LCRX, LCRS, and LCRG) will be analyzed with a nano liquid chromatography-tandem mass spectrometry (nLC-MS/MS). Each sample will be run more than twice under the identical conditions. The operational instruments and detailed methods will be in the method section of the reference paper.^[45]^

### Statistical analysis with database searches

2.13

After at least 2 MS/MS data are obtained from each sample, protein identification will be performed with 2 complementary database search programs. Both Proteome Discoverer 1.4 (Thermo Fisher Scientific Inc., USA) and ProteinPilot 5.0 (SCIEX, USA) will be used to identify proteins from MS and MS/MS spectra. Each software program has its own unique analysis algorithm. Thus, it will be meaningful to compare the results from the 2 programs because it will reinforce the confidence of the identified proteins. At least 4 data files with identified proteins will be produced from each sample. Each data file will be individually sorted and filtered under the following conditions:

(1)dynamic modification option: deamidated (N-glycosylation)(2)peptide confidence levels: the peptide is significant only if (a) confidence levels are over 95%, or (b) confidence levels are below 95% in 2 runs but show significant MS/MS spectra.(3)proteins inclusion and exclusion: for Proteome Discoverer software, only the proteins with protein scores of 6.0 or higher will be included; for ProteinPilot software, only the proteins with the unused values of 2.0 or higher will be included. The rest of the identified proteins will be excluded from the results.

Starting with the significant data from the 2 software programs, only the peptides/proteins with N-glycosylation sites will be selected and used for the parent protein identification. These glycoproteins will be sorted and compared within each group (Xu, Stasis, and Gentleness). Then these proteins will be sorted into those that are identified in all LCE groups, all LCR groups, and only certain group(s). The resulting 6 N-glycoprotein lists will be used for the following 5 comparative analyses:

(1)the glycoprotein comparison sets from the first and second MS/MS runs for the confirmation of reproducibility(2)the glycoprotein comparison sets from the 2 protein search engines to increase the confidence level of identified proteins(3)the glycoprotein comparison sets between LCE groups and LCR groups to check the representativeness(4)the unique and intersection glycoproteins set by comparison of LCE groups (LCEX, LCES, and LCEG) based on their pattern identifications assessed from BCQs of the lung cancer patients(5)the unique and intersection glycoproteins set by comparison of LCR groups (LCRX, LCRS, and LCRG) based on their pattern identifications assessed from BCQs of the lung cancer patients.

The overall data processing and analysis procedures are described in Figure 2. Unique glycoproteins from each group with each pattern identification of lung cancer patients will be generated from the results.

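### Proteins are identified and score-filtered file by file, and pattern-unique glycoproteins are then read from protein-level lists, so peptides shared by related proteins can create false unique calls

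*Protocol article*

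**What the plan says.** All of this is in the protocol article, section 2.13 (Statistical analysis with database searches), unless another section is named.

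- **Order of steps.** "After at least 2 MS/MS data are obtained from each sample, protein identification will be performed with 2 complementary database search programs". The output already consists of protein calls: "At least 4 data files with identified proteins will be produced from each sample".
- **Filtering.** "Each data file will be individually sorted and filtered under the following conditions". Two of the conditions work at protein level. For Proteome Discoverer, "only the proteins with protein scores of 6.0 or higher will be included". For ProteinPilot, "only the proteins with the unused values of 2.0 or higher will be included". Proteins below the floor are dropped.
- **Parent proteins.** After filtering, and starting from the significant data of both programs, "only the peptides/proteins with N-glycosylation sites will be selected and used for the parent protein identification".
- **Consolidation.** "These glycoproteins will be sorted and compared within each group (Xu, Stasis, and Gentleness". Six N-glycoprotein lists result.
- **Comparisons.** Five follow: (1) between runs, (2) between search programs, (3) between the entire (LCE) and representative (LCR) groups, (4) "the unique and intersection glycoproteins set by comparison of LCE groups (LCEX, LCES, and LCEG", and (5) the same for the three LCR groups.

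**The concern.** The measured unit is the peptide, but the unit compared between patterns is the protein. A peptide whose sequence occurs in several isoforms or homologous proteins does not by itself identify one parent. When proteins are called and filtered within a file, the parent that is listed, and whether it clears the floor, can depend on the other peptides found in that file. Two pools can then hold the same shared glycopeptide and still differ in the protein list: the parent is A in one and B in the other, or it passes 6.0 in one and falls just short in the other. Comparisons (4) and (5) would count either case as a difference between patterns.

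Comparison (2) has a related weakness. Section 2.13 itself notes that the two programs use different algorithms. Disagreement on protein names therefore need not mean disagreement on the peptides behind them.

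The pattern-unique proteins are the main product of the study. They carry primary outcomes 2 and 3 (section 2.2.1), and the Discussion intends to use the identified proteins as indicators of pattern identification.

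**Working it through.** **Step 1: the plan's own count.** Inputs from 2.13: at least 2 runs and 2 programs per sample. Files per sample = 2 × 2 = 4, which reproduces the stated minimum of 4. Over six pools (2.12) this is 4 × 6 = 24 files. Section 2.12 says that each sample is run more than twice. Read literally, that gives at least 3 × 2 = 6 files per sample and 36 in all. The two sections should be reconciled, but the point here does not depend on which holds.

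**Step 2: what is fixed per file and what is not.**

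| Step in 2.13 | Level stated |
|---|---|
| Protein identification | each run and each program |
| Peptide confidence rule and protein floors (6.0; 2.0) | each file |
| Parent-protein identification from N-glycosite data | not stated to be per file, and not stated to be joint |
| First comparison of glycoproteins | within a pattern |
| Unique and intersection sets | between pools, on protein-level lists |

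Comparisons (1) and (2) need a separate glycoprotein set for each run and each program, so such sets must exist at some stage. The only stated consolidation works within a pattern, whereas uniqueness is claimed between patterns.

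**Step 3: can a size be given?** Only under assumptions that are not in the document. Take one shared peptide detected in all three pools, with two possible parents, A and B. Let each naming event give A with probability q, independently.

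*Assumption (i): one name per pool.* The chance that some name appears in exactly one pool is 1 − q³ − (1 − q)³.

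*Assumption (ii): each pool's list is the union of its four files.* A is absent from a pool with probability a = (1 − q)⁴, and B with probability b = q⁴. The chance that some name appears in exactly one pool is 3(1 − a)a² + 3(1 − b)b². The two terms add because both events cannot occur together.

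| q | (i) one name per pool | (ii) union of four files |
|---|---|---|
| 0.5 | 1 − 0.125 − 0.125 = 0.75 | 2 × 3 × 0.9375 × 0.0625² = 0.02 |
| 0.7 | 1 − 0.343 − 0.027 = 0.63 | 0.0002 + 3 × 0.7599 × 0.2401² = 0.13 |
| 0.9 | 1 − 0.729 − 0.001 = 0.27 | about 0 + 3 × 0.3439 × 0.6561² = 0.44 |
| 1 | 0 | 0 |

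The ordering over q = 0.5, 0.7 and 0.9 reverses between the two columns. The result depends on q, on independence and on how files are merged, and the article gives none of these. Nor does it give the number of protein families seen only through shared peptides. The table shows that the mechanism can matter or can vanish. It is not an estimate for this study.

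**Step 4: under one common grouping.** If one rule names the shared peptide alike in every pool (q = 1), the chance of a naming-only unique call is 0 for a peptide found in all three pools.

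**The case against.** The strongest reply is that the gap is silence in a condensed article. Rules for shared peptides and protein groups are software settings that may sit in a fuller document. The processing flow is said to be in Figure 2, which is not shown. This stands as a reason to word the point as a risk. It does not remove the point, because the article does fix the order: proteins identified and filtered per file, then protein lists compared. Sections 2.10 to 2.12 defer detail to reference papers, whereas 2.13 defers none and goes down to numeric floors.

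Three stronger readings are tempting, and the document does not support them.

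- A reader might infer that every file is turned into its own parent-protein list. The per-file wording governs the filter conditions. The parent-protein step comes later, from the data of both programs, and six lists result.
- A reader might infer that false unique proteins arise even when pools hold identical peptides. If the program's choice is deterministic and the evidence is the same, the name is the same and the effect is zero. The concern needs pools that differ in their other peptides, or a choice that varies.
- A reader might take 75% as the size. It rests on an assumed q, on independence and on one name per pool. A union of four files gives about 2% at the same q.

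A further reply is that existing checks help. Naming that varies at random between files would show in comparisons (1) and (2). That is fair. A naming difference that is stable within a pattern would not show there. Nor would comparison (3) be likely to reveal it, because the LCR groups are drawn from the LCE groups (2.7.3) and processed the same way.

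**Conclusion.** The point holds as a risk built into the stated order of analysis. Protein calls and protein floors are applied in each of at least 24 files, and uniqueness is decided on protein-level lists, with neither joint grouping nor peptide-level confirmation stated. A shared peptide can then yield a false pattern-unique protein through naming or through the floor, and comparison (2) can mix naming with real disagreement between programs.

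This rests on two assumptions: that some N-glycosite peptides are shared by related proteins, and that pools differ in the other peptides found. The size is unknown and may be zero. The trial is described as preliminary (2.8), but its unique lists feed two of the three primary outcomes, so the change should be made before those lists are interpreted.

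**What to change.** 1. Within each program, process all runs of all six pools together, form one common set of protein groups, and read presence per pool from that set.
2. Call a protein pattern-unique only if it is supported by at least one N-glycosite peptide that is not shared with any protein listed in another pool.
3. In comparison (2), compare the two programs on peptides or protein groups instead of protein names.
4. State in 2.13 at which stage, and over which files, parent proteins are assigned.

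The cost is reprocessing of the existing raw files, with no new samples. Some isoform-level calls will merge into groups, and the unique lists will be shorter.

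### Peptide rule (2)(b) weakens the 95% threshold: it has no lower limit and a circular criterion, and false entries tend to gather in the unique-protein lists

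*Protocol article*

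**What the plan says.** All of this stands in section 2.13 of the protocol article.

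- **Unit of filtering.** "Each data file will be individually sorted and filtered under the following conditions". For the number of files: "At least 4 data files with identified proteins will be produced from each sample", that is, at least two runs searched with two programs.
- **Peptide rule (2).** Branch (a): "the peptide is significant only if (a) confidence levels are over 95" per cent. Branch (b), joined by *or*: "confidence levels are below 95% in 2 runs but show significant MS/MS spectra".
- **Protein rule (3).** For Proteome Discoverer, "only the proteins with protein scores of 6.0 or higher will be included"; for ProteinPilot, "only the proteins with the unused values of 2.0 or higher will be included". Other proteins are dropped.
- **List building.** "Starting with the significant data from the 2 software programs", peptides and proteins with N-glycosylation sites are kept and traced to their parent proteins. This gives six lists, one per pool.
- **Use of the lists.** Five comparisons follow. The first is "the glycoprotein comparison sets from the first and second MS/MS runs for the confirmation of reproducibility". The second compares the two engines, the third compares the entire (LCE) with the representative (LCR) groups, and the fourth and fifth extract unique and shared glycoproteins across Xu, Stasis and Gentleness. The stated end product is the set of glycoproteins unique to each pattern group. The Discussion says the identified proteins will be categorised as pattern indicators (biomarkers).

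**The concern.** An acceptance rule should tell two analysts with the same files to keep the same peptides. Branch (b) does not. It makes a peptide significant when its spectra are significant, without saying what that means, and it sets no confidence below which a peptide is refused.

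This matters because of how the result is formed. A protein is assigned to a pattern by presence in one list and absence from the other two. A true protein common to all patients will usually appear in all three lists. A mistaken identification with a small chance of arising in any one pool will usually appear in only one, so it looks like a pattern-specific protein. An error share that is harmless in a full list can be a large part of a unique list, and the unique lists are what would be carried forward as candidate markers.

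**Working it through.** The document states no error rate for its lists, so there is no figure to reproduce. Steps 1 and 2 use the text only. Steps 3 and 4 use assumed rates to show direction.

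**1. Reading the rule.** With (a) or (b), a peptide at any confidence below 95% can pass if it is seen in two runs and its spectra are called significant. For such peptides 95% is not a floor. Branch (b) also needs two runs, while the filter is applied file by file, so it cannot be carried out on a single file as written.

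**2. Do the other safeguards close the gap?**
- *Protein floors (6.0 and 2.0).* These act on the protein. Entry to a glycoprotein list depends on the peptide carrying the N-glycosylation site. On the text, a protein could clear its floor on other peptides while its glycosite peptide enters through branch (b).
- *N-glycosylation filter.* This selects by modification, not by confidence.
- *Run and engine agreement.* These are comparisons (1) and (2). Neither is stated as a condition of entry.

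**3. What does the two-run condition buy?** Assume that confidence c is the probability that an assignment is right, and ignore the spectral condition, whose effect is unknown. The chance that both assignments are wrong is (1 − c)² if run errors are independent and 1 − c if they are fully shared. Both runs use the same pool under identical conditions (section 2.12), so some sharing is plausible.

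| c in both runs | independent | fully shared |
|---|---|---|
| 94% | 0.06² = 0.4% | 6% |
| 80% | 0.20² = 4% | 20% |
| 50% | 0.50² = 25% | 50% |
| 20% | 0.80² = 64% | 80% |

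Just under 95% the condition helps. At low confidence, or with shared errors, it helps little.

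**4. Why errors gather in unique lists.** Let f be the chance that a protein appears in any one of three lists, independently. Then P(in exactly one list, given in at least one) = 3f(1 − f)² / [1 − (1 − f)³].

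- False protein, f = 1%: 0.029403 / 0.029701 = 99%. At f = 5% it is 95%, and at f = 10% it is 90%.
- True common protein, detected with probability 90%: 0.027 / 0.999 = 2.7%. At 80% it is 9.7%, and at 95% it is 0.7%.

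Now assume 100 true common proteins, 1000 possible false ones, detection d, no real group difference, and a false share s in each list. Per list:
- true proteins that look unique: 100 × d × (1 − d)²
- false proteins: F = 100 × d × s / (1 − s), of which F × (1 − F/1000)² look unique

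For d = 90% and s = 1%: true 100 × 0.9 × 0.01 = 0.90; F = 90 × 0.01 / 0.99 = 0.91, of which 0.91 look unique. The false share of the unique list is 0.91 / (0.91 + 0.90) = about 50%.

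| d | s = 1% | s = 5% |
|---|---|---|
| 80% | 20% | 57% |
| 90% | 50% | 84% |
| 95% | 80% | 95% |

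**The case against.** The strongest reply is that the rule has more protection than its wording suggests. Branch (b) is conditional on two runs and a spectral requirement, and the protein floors and the glycosite filter follow. Reproducibility and engine agreement are examined. Section 2.7.4 adds that comparing entire with representative groups will be used to validate the unique proteins. Those pools are prepared and run separately, so a random error would tend not to recur. The study also calls itself preliminary (section 2.8).

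Much of this stands, and it rules out several stronger readings:

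- *That branch (b) cancels branch (a).* It weakens it; the conditions above remain.
- *That spectra are judged by eye with the group known.* The article says neither. Coding the pools is a precaution, not the correction of a stated practice.
- *That a count of false unique proteins can be given.* One might take an error rate per file and add it over four files: 1% or 5% would become 1 − 0.99⁴ = 3.9% or 1 − 0.95⁴ = 18.5%. That needs the list to be the union of the files, which is not stated, and independent errors, although both engines search the same runs. Errors that never repeat would also seldom satisfy a two-run rule.
- *That no false discovery rate is used.* None is stated here, but section 2.12 leaves detailed methods to a reference paper, and Figure 2 is not shown. Its absence from the article is not a finding in itself.

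Two further limits apply to step 4. Errors shared across pools would land in the common set, not the unique one. And where a protein clears its floor on sound peptides, the error lies in its glycosite, not in its presence.

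The reply does not repair branch (b). The article chose to state the acceptance rule, and as stated it has no limit and no usable criterion. The planned comparisons describe agreement; they are not stated to remove a protein from a list. The entire and representative pools of one pattern also share patients' plasma.

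**Conclusion.** The point holds as a defect in a stated rule. Branch (b) admits peptides below 95% with no lower limit, on a circular criterion, and cannot be applied to files filtered one at a time. The later filters do not bound the confidence of the peptide that determines list membership.

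The direction of the harm follows from the presence-or-absence design, provided that false identifications have a low chance of arising in any one pool and are not strongly shared between pools. Its size is not known. The 20% to 80% range at a 1% false share, and the 57% to 95% range at 5%, rest on assumed list size, detection and false share and on no true group difference. They illustrate the mechanism and do not estimate this study's error. How much branch (b) itself adds depends on how often it is used, which the document does not say. The change should be made, but the study does not stand or fall on it.

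**What to change.** 1. Remove branch (b) from the lists used in comparisons (4) and (5). Report peptides that would have entered through it in a separate table, with their confidence in each run.
2. Make a prespecified false discovery rate the acceptance rule in each program, for example 1% by target-decoy search at peptide and at protein level, computed on the merged runs of each pool. If the reference paper already fixes one, state it here. Computing it on merged runs also removes the conflict between a two-run rule and file-by-file filtering.
3. Code the pools so that anyone judging spectra does not know the pattern group.
4. Report the unique lists also restricted to proteins found by both engines, as a sensitivity analysis and not as an entry requirement.

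Agreement should not be compulsory because lower detection creates its own false uniqueness. A protein present in all three pools appears in exactly one list with probability 3p(1 − p)². At p = 0.90 this is 2.7%. If both engines must find it, each at 0.90 and independently, p = 0.81 and it is 3 × 0.81 × 0.19² = 8.8%. For an assumed 200 common proteins, that is a rise from about 5 to about 18.

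The cost is a search setting, a coding step and a few protocol sentences. The downside is fewer reported proteins and somewhat lower detection, which can itself make some common proteins look unique.

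### The run-to-run reproducibility check is biased, because peptide rule (b) admits low-confidence peptides on the basis of two runs before the runs are compared

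*Protocol article*

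**What the plan says.** The relevant text is in Protocol section 2.13, Statistical analysis with database searches, unless another section is named.

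- **Unit of filtering:** "Each data file will be individually sorted and filtered under the following conditions".
- **Peptide rule (a):** "the peptide is significant only if (a) confidence levels are over 95" per cent.
- **Peptide rule (b)**, joined to (a) by *or*: "confidence levels are below 95% in 2 runs but show significant MS/MS spectra".
- **Protein cut-offs:** for Proteome Discoverer, "only the proteins with protein scores of 6.0 or higher will be included"; for ProteinPilot, "only the proteins with the unused values of 2.0 or higher will be included".
- **What goes forward:** "Starting with the significant data from the 2 software programs, only the peptides/proteins with N-glycosylation sites will be selected".
- **Use of the lists:** "The resulting 6 N-glycoprotein lists will be used for the following 5 comparative analyses". The first of the five is "the glycoprotein comparison sets from the first and second MS/MS runs for the confirmation of reproducibility".

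On the number of runs, section 2.12 has every sample run more than twice. Section 2.13 asks for at least two MS/MS data sets and at least four data files per sample.

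**The concern.** A check of reproducibility should let the two runs speak independently and then ask how often they agree. Here part of the material is admitted because of what two runs showed together, and the agreement of runs is then reported as a finding. No sentence in section 2.13 takes the peptides admitted by rule (b) out of comparison (1).

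Comparison (1) is the only one of the five that sets repeat runs of the same pool against each other. Comparison (2) contrasts search programs. Comparison (3) contrasts the entire and representative groups, and the latter are drawn from the former (section 2.7.3). The end product is a set of glycoproteins called unique to Xu, Stasis or Gentleness, which are calls of presence or absence. A glycoprotein missed in one run by chance can look like a difference between patterns, so readers will look to comparison (1) to judge how often that happens. A figure that the filter has partly produced is weaker support than it appears.

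**Working it through.** The protocol states no agreement figure, so there is none to reproduce. The check traces the rules and then illustrates their effect with assumed counts.

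**Step 1: trace each pair of run outcomes, with two runs and the rules applied file by file.** H means confidence over 95%, L means below 95% with an acceptable spectrum, 0 means not found.

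| Run 1 / run 2 | Result | Scored in comparison (1) |
|---|---|---|
| H / H | kept in both by (a) | shared |
| H / 0 | kept in one by (a) | not shared |
| L / 0 | kept in neither | not counted |
| L / L | kept in both by (b) | shared, by construction |
| H / L | kept in the H run by (a); fails (a) in the other, and (b) does not apply | not shared |

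A low-confidence peptide seen in one run only (L/0) is left out of the total, while its counterpart seen in both (L/L) is counted as shared. Peptides entering through (b) can therefore add to agreement but never to disagreement.

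**Step 2: effect of (b) on agreement at peptide level.** Take agreement as shared/total distinct, s/t under rule (a) alone. Adding m peptides through (b) gives (s + m)/(t + m). The change is m(t − s)/[t(t + m)], which is never negative.

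Assumed counts: s = 100 in both runs and 60 in one run only, so t = 160.

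- m = 0: 100/160 = 0.625
- m = 5: 105/165 = 0.636
- m = 20: 120/180 = 0.667
- m = 40: 140/200 = 0.700
- m = 80: 180/240 = 0.750

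**Step 3: range under assumed detection probabilities.** Let p be the chance of H and q the chance of L in a run, with runs independent. Agreement is p²/[1 − (1 − p)²] under (a) alone and (p² + q²)/[1 − (1 − p)² + q²] under (a) or (b).

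| p | (a) alone | (a) or (b), q = 0.1 | (a) or (b), q = 0.3 |
|---|---|---|---|
| 0.3 | 0.09/0.51 = 0.176 | 0.10/0.52 = 0.192 | 0.18/0.60 = 0.300 |
| 0.5 | 0.25/0.75 = 0.333 | 0.26/0.76 = 0.342 | 0.34/0.84 = 0.405 |
| 0.7 | 0.49/0.91 = 0.538 | 0.50/0.92 = 0.543 | 0.58/1.00 = 0.580 |

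The rise runs from about 0.5 points (0.543 − 0.538) to about 12 points (0.300 − 0.176).

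**Step 4: from peptides to glycoproteins.** Comparison (1) is made on glycoproteins, after the cut-offs of 6.0 and 2.0. A glycoprotein is affected only if its place on a run's list rests on peptides admitted by (b) and it also clears the score cut-off. The documents do not say how many do, so the figures above cannot be carried over.

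**Step 5: can (b) be applied as described?** Rule (b) needs the result of a second run. A filter applied to each data file on its own does not have that result. The two instructions conflict.

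**Step 6: which runs?** At least two runs with two programs give 2 × 2 = 4 files, as section 2.13 says. More than two runs, as section 2.12 says, give at least 3 × 2 = 6. With a third run, the two runs that satisfy (b) need not be the first and second runs of comparison (1), and concordance is then no longer guaranteed.

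**The case against.** The strongest reply is that a peptide entering through (b) was observed twice with an accepted spectrum, so its agreement is real evidence. That is fair as far as it goes. The bias lies in the selection of the total: the low-confidence peptides seen once, which would count against agreement, are never on a list.

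It can also be said that the effect may be slight. The share entering through (b) is not given, the protein cut-offs may absorb much of it, and the assumed grid goes down to half a point. The study is described as preliminary, no threshold or decision hangs on comparison (1), and section 2.7.4 assigns validation of the unique glycoproteins to the comparison of entire with representative groups. All of this stands and limits the consequence. It does not remove a built-in bias from the only check between runs.

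Three stronger readings are tempting, and the documents do not support them.

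- A reader might infer that rule (b) drops better-supported peptides, since one at 99% and 90% can be lost from a run while one at 60% in both stays. Because (a) and (b) are joined by *or*, (b) can only add. The 90% result is lost through the 95% cut-off in (a), and would be lost without (b). If significance is instead a verdict on the peptide as a whole, it is not lost at all.
- A reader might infer that the agreement says nothing about reproducibility. Peptides passing (a) can be judged within each run, and their overlap remains informative.
- A reader might infer that six lists, one per pool, make comparison (1) impossible. At least four individually filtered files per sample give 6 × 4 = 24 files by run and program. The reference to six lists is loose wording.

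**Conclusion.** The point holds in a limited form. Comparison (1) is a biased measure of run-to-run reproducibility, because the data it compares have been filtered by a rule that itself uses two runs. Where those are the two runs compared, peptides admitted by (b) agree by construction, and glycoproteins that depend on them count as reproduced. Rule (b) is also incompatible with filtering each file on its own.

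At peptide level, (b) can only raise agreement relative to (a) alone. At glycoprotein level the size is unknown; the illustrations rest on assumed counts and on independent runs. The conclusion assumes that the two runs in (b) are the first and second runs of comparison (1). It rests on the text of section 2.13. Figure 2, the flow chart of the processing, was not available and should be checked for an exemption that the text does not mention.

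This should be corrected before the agreement is reported, but it does not invalidate the comparison.

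**What to change.** - Make comparison (1) on run-level lists, separately for each run and program, filtered by condition (2)(a) and the protein-score cut-offs but without (b), before lists are merged to one per pool.
- For each pool, report shared and total counts, and how many peptides and glycoproteins enter only through (b).
- If (b) is kept, confine it to the merged pool lists, and reword it so that it does not conflict with filtering each file individually.
- Reconcile the number of runs in sections 2.12 and 2.13, and name the runs to which (b) and comparison (1) refer.

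The cost is re-sorting of files that will exist anyway and a few changes of wording; no new runs or samples are needed. The reported agreement will probably look somewhat lower. Peptides just above 95% in one run and just below it in the other will still count as discordant, and the report should say so.
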